### Analysis of Outcomes

#### Overview

The primary goal of the pilot randomized controlled trial is to evaluate feasibility and acceptability for a potential efficacy study using recruitment and retention rates and the Client Satisfaction Questionnaire–8. In addition to the primary goal, this study will also assess several primary, secondary, and exploratory outcomes. We are aware that we may be underpowered for the following analyses.

#### Primary and Secondary Outcomes

Primary and secondary outcomes will be tested using mixed-effects models [64,66]. This method allows for the inclusion of participants with missing data and those who dropped out without relying on data imputation. It provides an estimate of the individual variability around the population trend and the variability of the individual intercepts (baseline values) and slopes (changes across time and the correlation between them). A fully saturated treatment by visit model will be used for inference. Covariate structure will be chosen based on the Akaike information criterion. Data will be analyzed for all participants who were randomized for whom we have a baseline assessment and at least one follow-up assessment. We expect the dropout rate to be <10% after the baseline assessment (this dropout rate is considered in our power analysis estimation).

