**Methods:**

A pilot randomized controlled trial with 50 veterans randomized into 2 groups will be conducted. Participants will be recruited from the Veterans Affairs San Diego Healthcare System. Veterans with SMI and past-1-month active suicide thoughts or past-3-month suicide behavior as defined by the Columbia–Suicide Severity Rating Scale will be included. Enrolled veterans will be randomized to receive SUPPORT or enhanced standard care. All veteran participants will be assessed at baseline and the 1-, 2-, and 3-month follow-up assessments. Feasibility is defined as attainment of recruitment goals and a ≥70% retention rate. Acceptability for veterans is measured using the Client Satisfaction Questionnaire–8. Acceptability for peer specialists is measured using a satisfaction question rated on a 5-point Likert scale. Primary outcomes are measured using the Recovery Assessment Scale–41 (personal recovery), as well as the Beck Scale for Suicide Ideation and the Columbia–Suicide Severity Rating Scale (suicide ideation severity). Secondary outcomes are measured using the Specific Level of Functioning Scale (functioning), the brief version of the World Health Organization Quality of Life Scale (quality of life), and a laboratory-developed self-knowledge task (suicide prevention strategy recall). Outcomes will be tested using mixed-effects models. Safety procedures for all participants are discussed.

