#### Veteran Participant Measures

Veteran assessments are conducted at baseline and the 1-, 2-, and 3-month follow-ups. Table 2 shows the veteran participant measures. The measures included assess a range of standard outcomes important in the prevention of suicide, as well as including 2 laboratory-developed measures to explore SUPPORT’s potential unique impact on suicide prevention.

The primary outcome of personal recovery is measured using the 41-item Recovery Assessment Scale, a self-report measure of personal recovery with 5 domains: personal confidence and hope, willingness to ask for help, goal and success orientation, reliance on others, and no domination by symptoms [46]. The other primary outcome is assessed using interviewer -administered assessments of the 19-item Beck Scale for Suicide Ideation [47] for past-week suicide ideation severity and the C-SSRS [21,25] for past-month suicide ideation severity.

**Table 2 table2:** Veteran participant measures at all time points.

Timing and domain		Measure	Outcome type

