### Veteran Participant Sample Size Determination

The sample size for the pilot randomized controlled trial was estimated using a previous method provided by Hedeker et al [64] and the Repeated Measures and Sample Size software. This minimum power estimation is based on a 5% attrition rate per time point, correlation of 0.5% of repeated measures, and medium to large effect sizes. A total sample size of 44 will yield a minimum of 80% power to detect a large effect size, defined as a between-group difference increasing linearly from 0 at baseline to 0.7 SD units at the last time point. A large effect size was chosen as this is a pilot feasibility study and is not intended to be powered to detect a small or medium effect [65].

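### The stated 80% power at N=44 is not delivered by any usual contrast of the saturated model with free baseline means (about 47–64%; 53–70% at N=50); constraining baseline means recovers 11 to 14 points at N=50

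*Protocol article*

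**What the plan says.** Sizing (Veteran Participant Sample Size Determination): "A total sample size of 44 will yield a minimum of 80% power to detect a large effect size". The effect is "defined as a between-group difference increasing linearly from 0 at baseline to 0.7 SD units at the last time point". The inputs are "based on a 5% attrition rate per time point, correlation of 0.5% of repeated measures, and medium to large effect sizes". Significance level, sidedness, covariance form and the contrast that was powered are not given.

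Analysis (Primary and Secondary Outcomes): "A fully saturated treatment by visit model will be used for inference". The same paragraph describes individual intercepts and slopes and leaves the covariance to an information criterion. It names no visit, contrast or degrees of freedom, and does not say whether the arms share a baseline mean.

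Design: "Veteran assessments are conducted at baseline and the 1-, 2-, and 3-month follow-ups", so there are four time points. The abstract's Methods plan 50 veterans in two groups. The overview of the outcome analyses makes feasibility and acceptability the primary goal and says that these analyses may be underpowered.

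**The concern.** The two sections describe different inferential objects. The sizing hypothesis is a single quantity, a difference that starts at zero and grows in a straight line. The analysis model has a separate mean for each arm at each visit, including baseline, and several tests can be drawn from it.

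A free baseline difference has a cost. The arms are randomised after the baseline assessment, so the true difference there is zero by design. Estimating it adds its sampling error to every change-from-baseline contrast.

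The stake is modest but real. Aim 2 uses these outcomes to help judge whether a larger trial is warranted. A null result would be read against a stated power of 80% that the described model does not have.

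**Working it through.** **Inputs from the article.** Differences of 0, 0.233, 0.467 and 0.7 SD at months 0 to 3. Retention of 0.95 per time point, so 1, 0.95, 0.9025 and 0.857. Correlation printed as 0.5%, read as 0.5. N = 44 (power statement) and 50 (planned).

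**Assumed.** SD 1, compound symmetry, monotone dropout, 1:1 allocation, two-sided 5%.

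**Hand check, month 3, N=44, no dropout (22 per arm).**
- Free baseline: the variance of a change is 2(1 − 0.5) = 1. SE = √(1 × 2/22) = 0.3015, and 0.7/0.3015 = 2.32. Power is 64%.
- Baseline constrained: the residual variance is 1 − 0.5² = 0.75. SE = √(0.75 × 2/22) = 0.2611, and 0.7/0.2611 = 2.68. Power is 76%.

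**With the stated dropout.** The information for the four visit differences is summed over dropout patterns (proportions 0.05, 0.0475, 0.0451, 0.857) and inverted. A contrast has noncentrality (effect/SE)². Power is the upper tail of the noncentral chi-square beyond 3.84 (1 df) or 7.81 (3 df).

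| | N=44 free | N=44 constrained | N=50 free | N=50 constrained |
|---|---|---|---|---|
| SE, month-3 contrast (effect 0.7) | 0.318 | 0.280 | 0.298 | 0.263 |
| SE, slope (effect 0.7/3 = 0.233) | 0.1006 | 0.0871 | 0.0944 | 0.0817 |
| Power, 3-df interaction | 47% | 60% | 53% | 66% |
| Power, month 3 | 60% | 71% | 65% | 76% |
| Power, linear | 64% | 76% | 70% | 81% |

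Because the assumed effect is exactly linear, the 3-df test has the same noncentrality as the slope: at N=50 free, (0.2333/0.0944)² = 6.11. It spreads this over three degrees of freedom. The constrained linear figure uses the generalised least-squares slope; fixed weights −3, −1, 1, 3 on the constrained means give 79%.

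**Can 80% at N=44 be reproduced?** Not two-sided with the stated attrition: the linear contrast needs N=66 with free baseline means and N=50 with them constrained. It is reproduced if attrition is ignored and baseline is constrained (trend, 81.4%, N=44 exactly). A one-sided 5% test with attrition gives 75–76% for the linear contrast with free baseline means, still short, and 85% with them constrained.

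**Sensitivity at N=50** (3-df, month 3, linear).
- AR(1) with 0.5: free 30%, 44%, 44%; constrained 50%, 64%, 67%.
- Correlation literally 0.005: free 29%, 39%, 43%; constrained linear 82%.
- Total dropout of 10%, in line with the analysis section's expectation: free 54%, 66%, 71%; constrained linear 82–83%.

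**Shape of the effect** (N=50, compound symmetry, months 0 to 3).

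| Differences (SD) | 3-df free | 3-df constrained | Constrained trend |
|---|---|---|---|
| 0, 0.7, 0.7, 0.7 | 70% | 89% | 87% |
| 0, 0.7, 0.7, 0.35 | 65% | 82% | 51% |
| 0, 0.7, 0.47, 0.23 | 56% | 70% | 24% |

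**The case against.** The strongest reply is that the article names a mean model, not a test. That stands. A reader might infer that the planned test has 53–65% power, that saturation is the cause, and that a linear-trend test should replace it. The article does not support this. A linear contrast can be taken from the saturated model itself and gives 70% at N=50. The further step to 81% comes from constraining baseline means, which is compatible with saturated follow-up means.

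Nor is saturation without benefit. The four weekly modules end at about month 1, the check-in calls come 2 and 4 weeks later, and no contact is scheduled before month 3, so waning is plausible. The second table shows what a trend test would then lose. The hypotheses in Objectives state no shape.

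The trial is also a pilot that admits low power, and an article may leave the choice of contrast to a fuller plan. This lowers the weight of the point. It does not reconcile an explicit claim of at least 80% with an explicit model that does not reach it. If baseline were meant to be handled by adjustment, power would lie near the constrained figures, but two-sided power at N=44 would still be at most about 76%.

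A reader might also infer a multiplicity problem, because ideation is measured by the Beck scale and by "the C-SSRS [21,25] for past-month suicide ideation severity" and can be read at three visits. The article states no rule that success on any scale or visit suffices, so no inflated error rate can be charged to it.

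**Conclusion.** The point holds as a mismatch between the power statement and the inferential model. With free baseline means, two-sided power for the stated effect is about 47–64% at N=44 and 53–70% at N=50, depending on a contrast that the article does not name. Constraining baseline means adds 11 to 14 points at N=50. It raised power for all three contrasts under every effect shape and both covariance forms tried.

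The absolute figures rest on compound symmetry with correlation 0.5, a two-sided 5% level and 1:1 allocation. Under AR(1) even the constrained trend reaches only 67%. The direction of the gain does not depend on these choices; the 81% does. The documents do not support requiring a linear-trend test.

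**What to change.** In Primary and Secondary Outcomes, state that the model has a separate mean for each arm at each follow-up visit and one common baseline mean, with baseline kept as a response. Name the single contrast that answers the sizing hypothesis. A linear trend matches the sizing assumption; a month-3 contrast or the 3-df test relies less on linearity or not at all. Report the visit-specific estimates whichever is chosen.

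In Veteran Participant Sample Size Determination, restate power for that contrast at the planned N, with significance level, sidedness, covariance form, attrition and the correlation printed correctly.

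The cost is a few sentences, with no new data or visits. Randomisation justifies the constraint, so it fits best when all randomised veterans with a baseline are kept in the model. It cannot apply to suicide prevention strategy recall, which is collected only at 2 and 3 months. The restated power may fall below 80%, which agrees with the article's own caution.

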Research screening is used to confirm eligibility. Research staff will be available on the same day to accept a “warm handoff” for screening as needed. For all veterans contacted for screening, a CSRE will be conducted subsequently by the on-call psychologist if their risk level has changed since their last documented CSRE. If the veteran is deemed to be at moderate or high risk, a suicide safety plan will be completed or reviewed and updated. If the veteran is eligible, they will be invited to participate in a separate informed consent meeting and then subsequently enrolled in the study. Following enrollment, veteran participants will complete a diagnostic and baseline assessment and then randomized to SUPPORT or enhanced standard care. Those randomized to the SUPPORT condition will be matched with a peer specialist participant based on the peers’ and veteran’s availability. Randomized matching and veteran preference were considered but deemed not to be feasible given the nature of the pilot design. As feasible, veteran preference for identity characteristics such as gender as well as shared lived experience will be considered in matching as is standard practice for VHA peer services. Veterans not eligible at any stage will receive standard mental health care referrals and a study-designed resource packet.

Specific to allocation of conditions, a computer-generated 50-participant randomization table for this study was created and will be maintained by the project’s biostatistician. The table includes no matching on baseline characteristics, 1 follow-up assessment as the minimum number of follow-up assessments needed to be considered as intention to treat, and completion of a minimum of 1 module of the intervention to be considered as intention to treat for those in the SUPPORT condition. After enrollment, the study coordinator emails the veteran participant’s unique identification number to the biostatistician, who then provides the study coordinator with the allocation. There is no masking due to the pilot feasibility and acceptability design. See Figure 1 for the veteran participant timeline flow.

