The exploratory outcomes are cognitive problems and strategy use, burdensomeness and belongingness, hopelessness, suicide behavior, service use, and peer impact. Cognitive strategy use is measured using 30 self-report items on memory and thinking strategies that have been successfully used with a population with SMI and designed to capture changes in the use of compensatory cognitive training skills [37], referred to as “learning strategies” in SUPPORT. Burdensomeness and belongingness, which, when they converge, according to the interpersonal theory of suicide [53], create suicide desire [54], are captured using a 15-item self-report measure. The Beck Hopelessness Scale is a 20-item true-or-false self-report measure that has been shown to be predictive of eventual suicide in psychiatric inpatients [55]. Suicide behavior is measured using the C-SSRS behavior section, and service use (ie, suicide-related emergency department visits and inpatient psychiatry stays, Veteran Crisis Line contacts, and outpatient visits) is captured via chart review. Finally, based on theories related to peer support [56-63] and the Peer Specialist Fidelity Measure–Veteran Version (previously used to establish fidelity in traditional VHA peer support programs [39]), we co-developed with our advisory boards a measure collected posttreatment to evaluate the peer impact of veterans receiving SUPPORT. This measure includes 17 Likert scale–rated items and 14 open-ended questions. Likert scale items are rated from 1 (not at all) to 5 (very much). These items will be summed to obtain a total score; a higher score indicates a higher impact of the peer specialist. Sample Likert scale items include the following: “How much did your peer specialist encourage you to be hopeful?” and “How much did you feel connected with your peer specialist?” Open-ended items are asked to better understand the Likert scale–rated items (eg, “What did you have in common with your peer specialist that helped you connect?”).

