#### Exploratory Outcomes

Due to focus on feasibility, recovery, suicide ideation, and functioning, as well as the low anticipated base rates of suicide behaviors and crisis service use and overall sample size, these analyses are exploratory. The pilot randomized controlled trial exploratory analyses are twofold: (1) to compare SUPPORT to enhanced standard care on cognitive strategy use, thwarted belonginess, perceived burdensomeness, hopelessness, rate of suicide behavior, and rate of crisis service use; and (2) to compare SUPPORT to enhanced standard care on the mediational effect of personal recovery on suicide ideation severity. Peer impact will be reported descriptively for those who received SUPPORT, including a deductive analytic approach [67] of open-ended responses to determine themes.

First, mixed-effects models will be conducted as described for the primary and secondary outcomes. Next, given our small sample size, mediators will be tested in separate models [68,69]. We define treatment mediators as mechanisms through which a treatment might achieve its effects. We will test the products of (1) the *a* path (the independent variable [condition] to the mediator [eg, 2-month follow-up personal recovery]) and (2) the *b* path (the mediator to the dependent variable [3-month follow-up suicide ideation severity]). This procedure is a variation of the Sobel test [70] that accounts for the nonnormal distribution of the *a*-*b* path through bootstrapping procedures. Significant mediation effects are indicated when the 95% CI of the indirect path (*a*-*b*) does not overlap with 0. We will test a full mediation model, with changes in the mediator (assessed at the 2-month follow-up) preceding changes in the outcome variable (assessed at the 3-month follow-up).

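### The one-follow-up minimum, read as written, drops from the arm comparison of suicide behavior and crisis service use any veteran whose event is followed by no assessment at all

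*Protocol article*

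**What the plan says.** Under Analysis of Outcomes, Primary and Secondary Outcomes, the article states: "Data will be analyzed for all participants who were randomized for whom we have a baseline assessment and at least one follow-up assessment".

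The Exploratory Outcomes section lists, among the comparisons of SUPPORT with enhanced standard care, "rate of suicide behavior, and rate of crisis service use". For the method it says "mixed-effects models will be conducted as described for the primary and secondary outcomes". It gives no separate analysis population.

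The allocation paragraph (Recruitment, Screening, and Enrollment Procedures, Veteran Participants) states a similar minimum for the trial as a whole: "1 follow-up assessment as the minimum number of follow-up assessments needed to be considered as intention to treat". It adds a condition for one arm only: "completion of a minimum of 1 module of the intervention to be considered as intention to treat for those in the SUPPORT condition".

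On data sources, Veteran Participant Measures says "Suicide behavior is measured using the C-SSRS behavior section", while service use "is captured via chart review". Table 2 lists both at all time points.

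**The concern.** For a self-report scale, a veteran with no follow-up has no post-baseline value to lose. An event outcome is different, because the event can itself be the reason that no follow-up exists. A rule that requires a follow-up assessment then makes the denominator depend on the outcome, and the most serious events are the likeliest to be lost.

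For crisis service use the rule would also discard information that the trial can obtain without the veteran being present. The one-module condition, if it is applied, adds an exclusion that exists in SUPPORT only, so the two arms would be filtered by different rules.

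These two rates are the only comparison of suicidal events by arm that the article describes. The safety procedures and the reports to the institutional review board would bring an event to light, but the article does not feed them into a comparison by arm. Anyone deciding whether a larger trial is warranted would look at these rates.

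**Working it through.** **Does the filter reach these outcomes?** The sentence defining the population stands under the primary and secondary outcomes. Three things carry it over: the exploratory models are to be run as described there; no other population is named; and the allocation paragraph sets a one-follow-up minimum for the trial. This is the natural reading, but it is an inference and not an explicit statement.

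**Who is removed?** Follow-ups are at 1, 2 and 3 months, and any one of them suffices. Only a veteran with none of the three is removed.

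**How many?** The article gives no figure for veterans with no follow-up, so I derive it from three inputs:
- 50 randomized (allocation paragraph);
- 5% attrition per time point (Veteran Participant Sample Size Determination);
- expected dropout below 10% after baseline (Primary and Secondary Outcomes).

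If veterans who drop out do not return, those lost by month 1 have no follow-up:
- Expected number: 50 × 0.05 = 2.5.
- Chance of at least one, if losses are independent: 1 − 0.95^50 = 0.92.
- Upper limit, if all the expected dropout came before month 1: below 50 × 0.10 = 5.

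**How sensitive is the arm difference?** The article expects low event rates but gives none, and states no allocation ratio. The counts and the 25:25 split below are my assumptions. The excluded veterans are placed in SUPPORT, and each is assumed to have had an event, so these cases show what could happen and not what to expect. Differences are SUPPORT minus enhanced standard care.

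| All randomized | Excluded | Analyzed | Difference, before → after |
|---|---|---|---|
| 3/25 (12.0%) v 1/25 (4.0%) | 2 | 1/23 (4.3%) v 1/25 (4.0%) | +8.0 → +0.3 points |
| 2/25 (8.0%) v 2/25 (8.0%) | 1 | 1/24 (4.2%) v 2/25 (8.0%) | 0 → −3.8 points |
| 2/25 (8.0%) v 2/25 (8.0%) | 2 | 0/23 (0%) v 2/25 (8.0%) | 0 → −8.0 points |

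The two-sided Fisher p-value in the first row is 0.61 with complete data and 1.0 after exclusion; in the last row it is 1.0 and 0.49. No significance test would separate the arms in either state. What changes is the descriptive picture, and at this sample size that is what will be read.

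**The case against.** Several points on the other side are sound.

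*The carry-over concerns models, not populations.* This is possible. Table 2 also lists chart review as a measure at every time point, so a chart extraction might itself count as a follow-up assessment for service use. If that is intended, nobody with an accessible chart is lost for that outcome and one sentence would settle it. The text does not say so.

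*Most attempts and admissions would not be lost.* This stands. Safety Procedures provides for continued engagement after a psychiatric admission, and Ethical Considerations lets veterans leave SUPPORT and continue assessments. A reader might infer that any event before the 1-month visit drops out. It does not: attendance at month 2 or 3 keeps the veteran in.

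*The loss is not large.* A reader might take the 70% retention criterion to mean that up to 0.30 × 50 = 15 veterans could be excluded. That criterion is a feasibility floor at the end of the intervention, and a veteran lost by then may already have had a follow-up.

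*The article does not say that suicide deaths go uncounted.* A reader might infer from the C-SSRS as the named source that behavior is captured by interview alone and that a death enters no outcome. The article does not say only, and its description of the C-SSRS as interviewer-administered concerns ideation. How deaths are classified may be settled in the full protocol.

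*Adding charted attempts to the behavior outcome could itself bias it.* This stands and shapes the fix. In SUPPORT, peers ask about suicide and write a health-record note at each appointment; enhanced standard care has no such contacts. The C-SSRS is given on the same schedule in both arms.

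*The outcomes are exploratory in an acknowledged underpowered pilot.* True, and it limits the priority. It excuses imprecision, but not a denominator that can depend on the event.

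**Conclusion.** The concern holds in a limited form. Read as written, the minimum removes from the comparison of suicide behavior and crisis service use any veteran whose event is followed by no assessment, chiefly an early death or complete loss. The expected number without any follow-up is about 2.5 of 50, and fewer than 5 on the article's own dropout expectation. Not all of them will have had an event. With few events, one or two such exclusions could erase an observed difference or create an apparent one.

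This rests on three assumptions: that the filter carries over to the exploratory outcomes, that early dropouts do not return, and that a chart extraction does not count as a follow-up assessment. The event counts are illustrative. The documents do not show that event rates will in fact be biased, or in which direction. The feasibility, acceptability and primary outcome analyses are not affected by this point.

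**What to change.** For suicide behavior and crisis service use only, replace the one-follow-up minimum, and the one-module condition if it was meant to apply, with all randomized veterans by assigned arm, from randomization to 3 months. Then:

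- **Crisis service use:** take it from chart review regardless of attendance, as far as consent allows chart access after withdrawal.
- **Suicide deaths:** count them as suicide behavior from whatever source they become known.
- **Non-fatal suicide behavior:** keep the C-SSRS as the main measure. Show by arm how many veterans have no follow-up interview, so that missing is not read as no event.
- **Chart-documented attempts:** report separately by arm as supplementary, not pooled with the C-SSRS.
- **Presentation:** give the number of veterans with at least one event over the number randomized in each arm.

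The cost is a few sentences in the analysis section and some added extraction within a chart review already planned. Data collection is projected to run until May 2027, so the change can still be made. Two drawbacks should be stated with the results: chart ascertainment may be more complete in SUPPORT because peers ask about suicide and document each appointment, and care received outside the health system may be missed.
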